To investigate factors that predict pain persistence in people with sciatica, we will use variable selection techniques followed by predictive modelling. First, we will perform filtering of the original variables by calculating the univariate associations (coefficients, 95% CI, p values) between variables and the outcome and between each other. We will select a subset of uncorrelated variables that are associated with the outcome and use them as input features in machine learning algorithms for high-dimensional, small data sets that will allow us to identify the most powerful predictors and assess model selection/predictive accuracy. During preprocessing, missing data will be examined, the mechanism of missingness will be inferred using hypothesis testing and visually assessed using a matrix of boxplots for all pairs of variables and the outcome, and, if appropriate, multiple imputation by chained equations will be used. Drawing from machine learning techniques for high-dimensional small data sets, we will use resampling and validation in the form of repeated cross-validation to perform a complete variable profiling to identify the most powerful predictors. Multivariate adaptive regression splines (MARS) with built-in feature selection and Decision Tree models known to work well on low sample sizes will be trained to predict the 3-month and 1-year outcome. Model performance will be estimated using five times repeated 10-fold cross-validation and compared with models trained on surrogate data.^73^ The latter benchmarking technique is appropriate for small data sets, where holding out a subset of data before the analysis to be used as a pseudo-independent test set is impossible. Instead, an artificial—surrogate data set, preserving the descriptive statistics but not any of the potentially real associations between the variables and the outcome of the original dataset, will be created and the performance of models trained on the actual and surrogate dataset will be compared. Models’ predictive performance will be reported alongside variable importance rankings. Model selection will be done to maximise the Mathews correlation coefficient for dichotomised outcomes and to minimise the root mean square error for continuous outcomes during cross-validation. Scalar metric estimations of predictive performance including accuracy (binomial test p value against the majority class prevalence), balanced accuracy and the area under the precision/recall curve will be reported alongside their 95% CI. Predictor importance will be assessed using model specific techniques, that is, the reduction in performance estimated by cross-validation when each predictor is removed for MARS and node impurity for tree-based methods. Variables’ influence on the predicted outcome both at the global and individual level will be quantified by the partial dependence plots and individual conditional expectation,^74^ respectively. These will show the average marginal effect on the prediction given a certain value of a predictor variable and provide model interpretability.

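### Models are benchmarked against one surrogate data set, which gives no null distribution; the only model-level p value named, a binomial test of accuracy, is valid per patient but insensitive

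*Protocol article*

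**What the plan says.** All of this stands in the Data analysis plan section of the protocol article, unless another section is named.

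- Estimation and benchmark: "Model performance will be estimated using five times repeated 10-fold cross-validation and compared with models trained on surrogate data".
- The surrogate is introduced in the singular, as an artificial data set "preserving the descriptive statistics but not any of the potentially real associations between the variables and the outcome of the original dataset". It stands in for a held-out test set, which the plan considers impossible at this size. The use made of it is that "the performance of models trained on the actual and surrogate dataset will be compared". No number of surrogates and no decision rule is given.
- Selection metric: "Model selection will be done to maximise the Mathews correlation coefficient for dichotomised outcomes and to minimise the root mean square error for continuous outcomes".
- Reported metrics for the dichotomised outcome: "accuracy (binomial test p value against the majority class prevalence", then "balanced accuracy and the area under the precision/recall curve will be reported alongside their 95% CI". The number of trials in the binomial test and the method for the CIs are not stated.
- The section on outcome measures makes continuous outcomes the basis of analysis and allows dichotomisation as an aid to presentation.
- The Predictor profiling part of the sample size section calls this work exploratory. It expects a 30%/70% split of 180 patients with 15% attrition, and states 81% power for d=0.5 with a univariate Wilcoxon-Mann-Whitney test.

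**The concern.** The second aim asks whether a mechanism-based approach can identify factors that predict persistence. A reader of the results will want to know whether a model does better than chance, and the article names two devices for that.

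The first is a comparison with one draw from a no-association world. A single draw shows neither how far chance results spread nor how often chance alone would do as well. The second is a p value for accuracy against always predicting the majority class. When 70% of patients are in that class, a predictor can separate the groups usefully and still hardly raise accuracy, because few patients cross the 50% predicted-probability line. The first device is passed too easily by an uninformative model, and the second is failed too easily by an informative one. Both can misdirect the hypotheses that this exploratory work is meant to produce.

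**Working it through.** **Inputs.** From Predictor profiling: 54 persistent and 126 resolved; 15% attrition leaves 54 × 0.85 ≈ 46 and 126 × 0.85 ≈ 107, so n = 153; d = 0.5; alpha 0.05. From the Data analysis plan: 10 folds, 5 repeats, so 153 × 5 = 765 predictions.

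**The plan's own figure.** A two-sided comparison of means with 46 and 107 patients and d = 0.5 gives 0.5/√(1/46 + 1/107) = 2.836, and power Φ(2.836 − 1.96) = 80.9%. The stated 81% is reproduced. (The Wilcoxon efficiency factor 3/π lowers it to about 79%, which does not matter here.) This figure concerns a single variable, not a model.

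**One surrogate.** If the variables carry no information, the real data set and a surrogate with the association removed are close to exchangeable, so the real model scores higher with probability about 1/2. A rank-based p value from B surrogates, (1 + number at least as good)/(1 + B), cannot fall below 1/2 when B = 1. Two independent simulations of repeated cross-validation with a dichotomised outcome agree: with no signal the real model beat its one surrogate in 45% to 51% of runs. With one real d=0.5 predictor among 50 candidates (logistic model, filter inside the folds) it won in 70%, so a win separates signal from none poorly. The exchangeability argument does not depend on the metric and so covers RMSE too, although no continuous outcome was simulated.

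**Binomial test, one score per patient.** The null accuracy is 0.70 (107/153 = 0.699 gives the same cut-off). The smallest count with one-sided exact P ≤ 0.05 is 117, and 117/153 = 76.5%.

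For the best attainable accuracy, let k independent normal predictors each have shift 0.5. They combine to D = 0.5√k. With prevalence 0.30 the optimal threshold is t = D/2 + ln(0.70/0.30)/D, and accuracy = 0.30 × Φ(D − t) + 0.70 × Φ(t). For k = 1: D = 0.5, t = 0.25 + 0.847/0.5 = 1.945, accuracy = 0.30 × 0.074 + 0.70 × 0.974 = 0.704. The ROC area of the same predictor is Φ(0.5/√2) = 0.64. Power is P(X ≥ 117) for X binomial with n = 153 and that accuracy:

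| k | best accuracy | power |
|---|---|---|
| 1 | 0.704 | 6% |
| 2 | 0.717 | 11% |
| 3 | 0.732 | 21% |
| 5 | 0.761 | 50% |
| 6 | 0.773 | 64% |
| 8 | 0.796 | 85% |

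These are ceilings, because a fitted model does not reach the optimal rule. In the simulations with five real d=0.5 predictors among 50 or 55 candidates and the filter inside the folds, a linear or logistic classifier passed the binomial test in 10% to 11% of runs. Judged by Matthews correlation against a null distribution, it was detected in 78% to 87%. With shallow trees the figures were 3% and 54%.

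**Validity.** With no signal and the filter inside the folds, the test on 153 patients rejected in none of the runs: average accuracy was 0.64 to 0.67, below the majority rate. With five real predictors (logistic), cross-validated accuracy averaged 0.717. The nominal SE is √(0.717 × 0.283/153) = 0.036 against an actual SD of 0.033, and the 95% CI covered 97%.

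**If the 765 predictions were pooled.** The nominal SE falls to √(0.717 × 0.283/765) = 0.016 while the actual SD stays at 0.033. Coverage drops to 69% (61% to 74% in the other simulation).

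**The case against.** Four points can fairly be made for the plan.

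- A reader might infer that the models stand or fall on these two devices. They do not. RMSE, Matthews correlation, balanced accuracy and precision/recall area are also named, and the binomial test applies only if the outcome is dichotomised, which the plan makes secondary. This stands. However, the article names no chance reference for those metrics other than the surrogate.
- A reader might infer that the binomial p value and the CIs are invalid. The article does not support that. With one score per patient the test is conservative and its interval covers. The trouble with 765 predictions depends on pooling that the article never states. Even pooled, with no signal and the filter inside the folds, the test rejected in at most 0.3% of runs. One simulation gave 16% pooled rejection, but in a setting with five real predictors whose accuracy happened to equal the majority rate; it is not a false-positive rate for uninformative variables.
- The d=0.5 belongs to a univariate calculation, no model accuracy was planned, and six or more such predictors would give reasonable power. The binomial and permutation tests also address different nulls: beating the majority rule, and any association at all. This stands, so the power figures describe how blunt the test is and do not show a missed design target.
- The single surrogate is read from a singular noun, the article also speaks of surrogate data, the cited method source is not at hand, and no p value is claimed from the comparison. This is why the point is limited to the plan as worded.

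The exploratory label lowers the stakes but does not turn one draw into a reference distribution.

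**Conclusion.** The point holds in a limited form. As worded, the surrogate benchmark is a single draw that an uninformative model beats about half the time, on either outcome scale. For dichotomised outcomes, the only model-level p value named is valid with one score per patient, but it has best-case power of about 6%, 21% and 50% with one, three and five independent d=0.5 predictors, rising to 64% and 85% with six and eight. These figures assume 153 completers, 30% prevalence, normality and independence. The simulated contrast further assumes 50 or 55 independent candidates, a p<0.05 filter, and linear, logistic or tree models; MARS was not simulated. Pooling of repeats is a risk that the wording leaves open and not something the plan says it will do. The change is worth making before analysis, as an improvement to an exploratory analysis.

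**What to change.** Extend the plan's own surrogate idea. Generate many surrogates, for example 1000 permutations of the outcome. In each, rerun the whole pipeline: univariate filter, any tuning, model fitting and repeated cross-validation. The filter must be rerun because it is described as a first step and is not said to sit inside the folds. In simulation, filtering on all the data gave uninformative logistic models a Matthews correlation of about 0.12, and surrogates put through the same filter showed the same optimism.

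Take the p value from the rank of the observed selection metric among the surrogates: RMSE for continuous outcomes, Matthews correlation if dichotomised. Keep accuracy as a descriptive figure beside the majority prevalence, without the binomial test as evidence of prediction. Compute any 95% CI with the patient as the unit, for example by resampling patients, and not over 765 predictions.

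The cost is a paragraph of wording and computing time: 1000 × 5 × 10 = 50,000 fits per model type, outcome and time point, before tuning. No new data are needed.

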### Primary mechanism-based prognostic variables

#### Self-reported sensory profiling

See table 1 for questionnaires. The Neuropathic Pain Symptom Inventory and PainDETECT will be used to determine sensory symptom clusters as previously reported.^25^ Patients will be instructed to report the localisation of pain, paraesthesia and hypoesthesia on separate body charts by means of pen-on-paper pain drawings (A4 sheets including ventral and dorsal view of female or male body). All drawings will be digitised and analysed using online software (https://syp.spslab.ch). The derived variables (ie, extent and location) will be used to describe the symptoms associated with sciatica at baseline. These have been shown to provide clues about central sensitisation^26 27^ and may predict clinical outcome in other conditions.^28 29^

**Table 1 T1:** Questionnaires

Questionnaires *primary outcome **secondary outcome		FORECAST patients		Healthy volunteers	Painstorm dataset
		Baseline	Follow-up	Baseline	Extended
FORECAST outcomes	Sciatica Bothersomeness Index (SBI)^21^	X	X*		
	Numerical Pain Rating Scale—previous 2 weeks (worst, least, average for leg /back pain)	X	X*		
	Global Rating of Change Scale		X**		
Neuropathy/neuropathic pain	PainDETECT^79^	X	X		X
	Neuropathic Pain Symptom Inventory (NPSI)^80^	X	X	X	X
	DN4^69^	X	X		X
	Michigan Neuropathy Screening Instrument (MNSI)^70^				X
Pain location, severity	Pain location—list of sites, body chart	X	X	X	X
	Monthly pain diary	X	X		
	Chronic Pain Grade (CPG)^71^				X
	Brief Pain Inventory (BPI)^72^				X
Disability	Oswestry Disability Index (ODI 2.1a)^57^ – Leg Pain	X	X**		
	Oswestry Disability Index (ODI 2.1a)^57^—Low Back Pain	X	X		
	Oswestry Disability Index (ODI 2.1a)^57^—combined leg and back pain			X	
Risk	Keele STarT Back tool^58^	X			
Lifestyle	International Physical Activity Questionnaire (IPAQ, long version)^81^	X	X	X	X
Quality of life	EQ-5D-5L (v1.2)^59^	X	X	X	X
Psychosocial questionnaires	PROMIS SF8a—Ability to participate in social roles and activities^43^ (v1.0)	X	X	X	X
	Pain Catastrophising Scale (PCS)^44^	X	X	X	X
	PROMIS SF8-a—Depression and Anxiety^43^ (v1.0)	X	X	X	X
	Adverse Childhood Events (ACEs) (none, 1, 2,>2)	X		X	X
	Prolonged hospitalisation for life-threatening condition (yes/no)	X		X	X
	PROMIS SF8a—Sleep Disturbance^43^ (v1.0)	X	X	X	X
	PROMIS SF8a—Fatigue^43^ (v1.0)	X	X	X	X
	PROMIS SF4a—instrumental support^43^ (v1.0)	X	X	X	X
	PROMIS SF4a—Emotional Support^43^ (v1.0)	X	X	X	X

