We will use healthy control data to calculate Z-scores, where each individual parameter is related to its region-specific, age-specific and gender-specific reference range. We will collect our own normative data, assisted by the provision of an existing QST dataset.^32^ Using a previously published algorithm,^13^ patients will also be assigned one of the following somatosensory profiles (1) sensory loss, (2) thermal hyperalgesia, (3) mechanical hyperalgesia.

Furthermore, we will include a conditioned pain modulation (CPM) paradigm to examine the efficacy of the descending pain modulatory system. Such dynamic QST protocols have shown most promising prognostic ability in other pain conditions.^15 16^ Based on current recommendations,^33^ we will evaluate a sequential CPM paradigm using PPT over the thenar eminence of the dominant hand (test stimulus, average of three repetitions) and cold-water immersion of the non-dominant hand to the level of the wrist (conditioning stimulus). This combination has provided the most reliable and large magnitude CPM effects.^34^ The water bath will be standardised to 4°C±2°C by adding ice. Patients are asked to report the intensity of pain experienced by cold water immersion from 0 (no pain) to 100 (worst pain imaginable). Once the pain reaches the cut-off of >40/100, or after a maximum of 2 min if this cut-off is not reached,^33 35^ the participants will be asked to remove the hand from the water bath. The test stimulus will be repeated immediately thereafter. Cold water immersion is the most used CPM conditioning stimulus and is easy to implement and seems to be the most effective CPM paradigm.^36 37^ PPT measurements are convenient, quickly measured and frequently used as a test stimulus.^38^ A good to excellent intrasession reliability for CPM assessment with PPTs has been reported.^37 39^

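### Ranking tree predictors by node impurity tends to favour many-valued variables over yes/no and few-level ones; held-out permutation importance removes most of this

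*Protocol article*

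**What the plan says.** All of this stands in the protocol article, mainly under Data analysis plan.

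- Candidates are filtered first: "We will select a subset of uncorrelated variables that are associated with the outcome and use them as input features in machine learning algorithms".
- MARS and tree models follow: "Decision Tree models known to work well on low sample sizes will be trained to predict the 3-month and 1-year outcome". Repeated cross-validation is used "to perform a complete variable profiling to identify the most powerful predictors".
- Importance is model-specific: "the reduction in performance estimated by cross-validation when each predictor is removed for MARS and node impurity for tree-based methods". As the sentence is built, cross-validation belongs to the MARS measure only.
- The rankings are an output: "Models’ predictive performance will be reported alongside variable importance rankings".
- The surrogate data set serves to compare the performance of models. It is not given a role as a reference for importance.

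The candidates differ widely in their number of distinct values. Table 1 lists a yes/no item on prolonged hospitalisation and a four-level item on adverse childhood events. Under Somatosensory profiling, "patients will also be assigned one of the following somatosensory profiles (1) sensory loss, (2) thermal hyperalgesia, (3) mechanical hyperalgesia". Beside these stand QST Z-scores, 17 cytokines/chemokines and NMR metabolites, all continuous.

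**The concern.** A tree picks, at each node, the cut with the largest drop in impurity, and the importance score adds up those drops on the same data. A yes/no variable offers one cut and a four-level ordered variable three. A continuous variable in 153 patients with a minimum leaf of 7 offers 153 − 2×7 + 1 = 140 at the root. The best of 140 cuts will show a larger drop by chance than the only cut available, even when the two variables are equally prognostic.

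The plan fixes this measure by name, so it is not a detail left open. It states no correction for the number of cuts and no null reference for importance. At stake is which variables appear at the top of the tree ranking, in a study meant to identify prognostic factors and to shape later validation studies. A few-level clinical or history item could be placed below a laboratory or QST variable of no greater prognostic value.

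**Working it through.** **Sample size.** The plan gives no figure for the importance measure. The only figure for this analysis is the 81% power under Predictor profiling, which fixes the numbers to use. With 54 and 126 patients and 15% attrition, n₁ = 54×0.85 = 45.9 and n₂ = 126×0.85 = 107.1, total 153.

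Power = Φ(d·√(n₁n₂/(n₁+n₂)) − 1.96) = Φ(0.5×√32.13 − 1.96) = Φ(0.874) = 80.9%. The stated 81% reproduces. With the Wilcoxon efficiency 3/π it is 79.1%.

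**Simulation.** The following are assumptions, since the article gives none of them:
- three independent predictors: one continuous, one binary (50/50), one four-level with equal quarters;
- outcome y = β(z₁+z₂+z₃) + e·√(1−3β²), with standardised z and e, so each predictor has true correlation β with y;
- β = 0 (no effect) or 0.25 (equal effects);
- a single tree with minimum leaf 7;
- filter: all three predictors pass p<0.05 univariately.

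Share of data sets in which each predictor ranks first (continuous / binary / four-level), continuous outcome:

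| Scenario | Measure | Rank-first share |
|---|---|---|
| No effect, depth 3 | impurity | 96 / 1 / 3% |
| Equal effects, depth 3 | impurity | 71 / 11 / 17% |
| Equal effects, filtered, depth 3 | impurity | 73 / 12 / 15% |
| Equal effects, depth 2 | impurity | 54 / 20 / 26% |
| Equal effects, filtered, depth 2 | impurity | 54 / 22 / 24% |
| Equal effects, depth 3 | impurity averaged over 10 training folds | 79 / 9 / 12% |
| No effect, depth 3 | held-out permutation | 37 / 34 / 29% |
| Equal effects, depth 3 | held-out permutation | 43 / 31 / 26% |

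An even-handed measure would give about 33% each. The first three rows use 1,000 to 2,000 data sets, the depth-2 rows 600, and the fold-averaged and permutation rows 300 (standard error about 3 points). Repeat runs at depth 3 put the continuous predictor first by impurity in 70–73% (equal effects) and 67–73% (filtered), and by held-out permutation in about 35–40%.

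With a dichotomised outcome at 30% prevalence and depth 3, impurity puts the continuous predictor first in 81% (equal effects) and 79% (filtered).

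**Reading.** The direction was the same in every impurity run. Neither the filter nor averaging impurity over training folds removes the tilt. Permutation leaves a small residue, because the tree itself still splits more readily on the continuous variable.

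**The MARS measure applied to trees.** Cross-validated removal at depth 3 with equal effects gives 10 / 51 / 39%. With unpruned trees it tilts the other way, so carrying the MARS measure over to trees is not a clean substitute.

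**The case against.** Several counter-arguments stand and limit the point.

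- **Filter and model selection.** The plan does not feed pure noise into a fixed tree. With nine noise variables, a p<0.05 filter passes about 9×0.05 = 0.45 on average. When depth 0 to 3 is chosen by cross-validated error, 81% of null data sets retain no tree. The no-effect figures thus show the mechanism and are not a forecast. The equal-effects figures carry the point.
- **Noise above real factors.** A reader might infer that continuous noise will be ranked above true binary factors. The material does not support this as a rule. In a test of one weak binary factor (60% vs 40% prevalence) against 10 continuous noise variables, impurity ranked the factor first in 14.5% of runs and held-out permutation in only 21.5%. Most of that shortfall is a weak signal at this sample size.
- **Psychosocial factors.** A reader might infer harm to this domain as a whole. Most of its measures are multi-item scores (the PROMIS forms, catastrophising, optimism, stigma) with many distinct values, which behave almost like continuous ones. If only such variables survive the filter, the tilt is small.
- **Two different measures.** A reader might object that the MARS and tree rankings cannot be compared. The plan openly calls them model-specific and nowhere pools them, so this is not an inconsistency.
- **Weight of the ranking.** The article also reports univariate coefficients with intervals, performance against surrogate data, partial dependence and the MARS ranking. Under Predictor profiling it calls the work exploratory.

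What does not stand is that these features cure the tree ranking. Where few-level and continuous variables both survive, the tilt remains.

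**Conclusion.** The point holds in a limited form: as written, the tree ranking tends to favour many-valued over few-level predictors. At equal true correlation of 0.25, a continuous predictor comes first in about 50–75% of data sets with a continuous outcome, and somewhat more often (81% at depth 3) with a dichotomised one. Filtering at p<0.05 leaves about 54–73% for the continuous outcome.

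The size rests on the assumed tree depth, leaf size, effect, category splits and filter threshold, and on single trees; ensembles were not examined. That impurity is computed in-sample is an inference from its definition and from the absence of any stated held-out version. Severity is minor to moderate.

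**What to change.** Replace node impurity for the tree models with permutation importance on the held-out folds. For example: for each tree model, importance is the rise in RMSE (continuous outcome) or fall in MCC (dichotomised outcome) when the predictor is permuted in the held-out data of the five-times repeated 10-fold cross-validation, averaged over repeats and shown against the same quantity from the surrogate data.

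A held-out fold has about 153/10 ≈ 15 patients and 46/10 ≈ 5 with persistent pain, so MCC is better computed on predictions pooled over the ten folds of each repeat. Conditional-inference trees, which choose the splitting variable without this preference, are an alternative.

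The cost is about one sentence and extra computing time, with no new data. The downside is noisier importance estimates, so close ranks should not be over-read.
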